### Covariates

The following covariates will be identified: age, year, ethnicity, stage (from cancer registry records), cancer treatment (including radiotherapy, chemotherapy and surgery, from cancer registry records), grade (from cancer registry records), relevant comorbidities (including Charlson comorbidity conditions, from hospital admissions in Scotland and GP records and hospital admissions in Wales), medication use (including aspirin, statins and other medications associated with cancer survival), hysterectomy/oophorectomy (from hospital admissions in Scotland and hospital admissions and GP records in Wales), family history of cancer (from GP records, not available in Scotland), deprivation (based upon the relevant Index of Multiple Deprivation [34, 35]) and smoking and Body Mass Index (BMI from GP records, not available in Scotland).

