### Statistical analysis

Two main analyses will be conducted investigating HRT use after diagnosis and immediately before diagnosis.

In the analysis of HRT use after diagnosis, patients will be followed from 6 months after cancer diagnosis to cancer-specific mortality (censored on death from other causes or end of follow-up). Consequently, patients who died from any cause in the first 6 months after cancer diagnosis will be excluded as it seems unlikely that HRT use after diagnosis could impact upon such deaths (in sensitivity analyses this duration will be varied, described later). HRT use will be modelled as a time varying covariate to avoid immortal time bias [36], i.e. patients will be considered non-users and then users after a lag of 6 months after their first HRT prescription. A lag is recommended in studies of medication use and cancer survival [37] as it moves the exposed period forward which is more likely to reflect when the medication will may have an impact. A dose-response analysis will be conducted by duration of use based upon daily defined doses (DDDs) and number of prescriptions. An individual will be considered a non-user prior to 6 months after first HRT use, a user of 0 to 1 year of prescriptions from 6 months after first prescription to 6 months after their 12th prescription (or 365th DDD) and a greater user after this time. Time-dependent cox regression models will be used to calculate hazard ratios (HRs), and 95% confidence intervals (CIs), for HRT use after cancer diagnosis adjusting for age, year, ethnicity, stage, cancer treatment, grade, comorbidities, prior hysterectomy/oophorectomy, medication use (as time-varying covariates) and deprivation. A two-stage analysis procedure using random effects models will be conducted to pool results across cohorts [38]. Separate analyses will be conducted by type and route of administration of HRT.

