In the analysis of HRT before diagnosis, cancer patients will be followed from diagnosis to cancer-specific mortality. HRT use will be identified in the 18 months before diagnosis excluding HRT use in the six months immediately before diagnosis, as depending upon the cancer drug use can increase in this period due to cancer symptoms [39]. Cox regression models will be used to calculate HRs and 95% CIs for cancer-specific death in HRT users compared with non-users. Age, year, ethnicity, comorbidities, prior hysterectomy/oophorectomy and medication use before diagnosis will be included in these cox regression models to calculate adjusted HRs and 95%CIs. Stage, grade and cancer treatments will be excluded from the models investigating HRT before diagnosis, as these could lie on the causal pathway. As before two-stage methods will pool results across cohorts.

A number of additional analyses will be conducted. First, the main analysis will be repeated additionally adjusting for characteristics not available in both cohorts e.g. family history, smoking and BMI (only available in Welsh data). An analysis will be conducted restricted to women over age 55 (i.e. post-menopausal women) and an analysis will be conducted widening the age groups to include younger women aged 18 to 40 (Scottish data). An analysis of HRT after diagnosis will be conducted using a new-user design i.e. restricting analyses to cancer patients who did not use HRT before diagnosis [40], and after adjustment for HRT before diagnosis. A separate analysis will be conducted investigating the timing of HRT initiation after cancer diagnosis. Analyses of HRT after diagnosis will be conducted varying the lag from 6 months to 1 and 2 years.

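### The pre-diagnosis HRT model omits deprivation without a stated reason, although it is a listed covariate in both cohorts and is adjusted for in the post-diagnosis model

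*Protocol article*

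**What the plan says.** All references are to the protocol article. The Statistical analysis section opens with "Two main analyses will be conducted investigating HRT use after diagnosis and immediately before diagnosis", so the pre-diagnosis analysis has main status.

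- **After diagnosis.** Besides age, year and ethnicity, the Cox model adjusts for "stage, cancer treatment, grade, comorbidities, prior hysterectomy/oophorectomy, medication use (as time-varying covariates) and deprivation".
- **Before diagnosis.** The adjustment set is given in one sentence: "Age, year, ethnicity, comorbidities, prior hysterectomy/oophorectomy and medication use before diagnosis will be included in these cox regression models".
- **Deliberate exclusions.** These follow at once, with a reason: "Stage, grade and cancer treatments will be excluded from the models investigating HRT before diagnosis, as these could lie on the causal pathway".
- **Availability.** The Covariates section lists "deprivation (based upon the relevant Index of Multiple Deprivation" among the variables to be identified. It marks family history, smoking and BMI as unavailable in Scotland, but puts no such limit on deprivation.
- **Additional analyses.** A further fit of the model is planned, "additionally adjusting for characteristics not available in both cohorts e.g. family history, smoking and BMI (only available in Welsh data").
- **Secondary outcomes.** The primary strategy is repeated for all-cause mortality and second cancers. The cardiovascular and VTE models concern HRT after diagnosis and adjust for the confounders already named.

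**The concern.** Deprivation is the only covariate of the post-diagnosis model that is missing from the pre-diagnosis model without explanation. By adjusting for it after diagnosis, the sponsor already treats it as a confounder of HRT use and cancer death. Area deprivation is a background characteristic, and the protocol does not name it as a possible mediator, so the reason given for dropping stage, grade and treatment does not extend to it.

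The main pre-diagnosis model also leaves out smoking and BMI, and in Scotland no sensitivity analysis can add them. Deprivation is then the most direct socioeconomic control that both cohorts hold. If HRT users are less deprived than non-users and deprived women have worse cancer survival, the hazard ratio would be pulled below its true value and HRT would look safer than it is. Pooling would not remove a bias that runs the same way in both cohorts. The same gap would pass to all-cause mortality and second cancers wherever the pre-diagnosis model is reused.

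**Working it through.** **1. The two adjustment sets side by side**

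| Covariate | After diagnosis | Before diagnosis | Reason stated for the difference |
|---|---|---|---|
| Age, year, ethnicity | yes | yes | none needed |
| Comorbidities | yes | yes | none needed |
| Hysterectomy/oophorectomy | yes | yes | none needed |
| Medication use | time-varying | before diagnosis | follows from the timing of exposure |
| Stage, grade, treatment | yes | no | possible mediators |
| Deprivation | yes | **no** | **none** |

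**2. Does another sentence restore it?** The extra-adjustment analysis is worded for characteristics that one cohort lacks, so it does not cover deprivation. The pre-diagnosis paragraph refers back to the post-diagnosis method only for pooling. The reference to confounders already mentioned belongs to the cardiovascular and VTE models.

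**3. The plan's own figures.** The Sample size calculation section covers HRT after diagnosis only. With D deaths, a proportion p of users and a two-sided 5% level, Schoenfeld power is Φ(|ln HR| × √(D·p·(1−p)) − 1.96). The inputs are p = 0.07, D = 6820 (colorectal) and D = 1181 (gastric).

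- Colorectal: √(6820 × 0.07 × 0.93) = 21.07. HR 1.15 gives Φ(0.1398 × 21.07 − 1.96) = 83.8%. HR 0.85 gives 92.8%.
- Gastric: √(1181 × 0.07 × 0.93) = 8.77. HR 1.45 gives 90.3%.

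All agree with the stated power of over 80%. The formula contains no covariate term, so adding deprivation changes none of these figures.

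**4. Possible size of the shift (assumptions, not document figures).** Take five equal deprivation groups, 7% HRT use overall, equal steps between groups, no true HRT effect and no other adjustment. With hazard h and use u in each group:

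factor = [Σu·h / Σu] ÷ [Σ(1−u)·h / Σ(1−u)]

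| HRT use, least to most deprived | Death hazard, least to most deprived | Mean hazard, users | Mean hazard, non-users | Factor |
|---|---|---|---|---|
| 8% to 6% | 1.0 to 1.2 | 1.0929 | 1.1005 | 0.993 |
| 9% to 5% | 1.0 to 1.3 | 1.1286 | 1.1516 | 0.980 |
| 10% to 4% | 1.0 to 1.5 | 1.1964 | 1.2540 | 0.954 |

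**5. Cross-check with one binary confounder.** The factor is [1 + p1(H − 1)] ÷ [1 + p0(H − 1)], where H is the hazard ratio for deprivation and p1 and p0 are the deprived shares in users and non-users. All three inputs are assumed.

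- H = 1.1, 35% v 40%: 1.035 / 1.040 = 0.995.
- H = 1.3, 30% v 40%: 1.09 / 1.12 = 0.973.
- H = 1.5, 20% v 40%: 1.10 / 1.20 = 0.917.

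The first two lie in or beside the range in step 4. The last needs the deprived share in users to be half that in non-users.

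**The case against.** **It is probably a drafting slip.** The Covariates section lists deprivation without restriction. The list of deliberate exclusions does not name it. The covariate sentence says what will be included, not that nothing else will be. The Abstract speaks of adjusting for relevant confounders and then of repeating the analysis for use before diagnosis. This reading is plausible, and it weighs against calling the omission a choice. It does not remove the point: the article spells out both lists and explains how they differ, and an analyst following the second list would leave deprivation out.

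**Size and direction are unknown.** This stands. The documents give no association of deprivation with HRT use or with cancer death. The factors above are crude, and two of the three main scenarios move the hazard ratio by 2% or less. The model also adjusts for comorbidity and medication, which may carry part of any deprivation effect.

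**The Welsh analysis adds smoking and BMI directly.** This is partly right. It tests some of the pathway, but it neither restores deprivation nor helps in Scotland.

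A reader might infer three stronger claims that the documents do not support:

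- *That confounding could account for about a third of the effect the study aims to detect.* This sets the extreme scenario (1 − 0.954 = 0.046) against 1 − 0.85 = 0.15. The 0.85 and the 7% use belong to the post-diagnosis calculation, and 0.85 to colorectal cancer alone. No target is stated for the pre-diagnosis analysis.
- *That the omission spoils a clean comparison of the two main analyses.* They already differ by design in start of follow-up, exclusion of early deaths, fixed or time-varying exposure, and adjustment for stage, grade and treatment.
- *That every secondary outcome is affected.* The cardiovascular and VTE models take up the confounders already named, which include deprivation.

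**Conclusion.** The point holds as an unexplained and avoidable gap in one of the two main models. Deprivation is listed for both cohorts, is used in the post-diagnosis model and is not among the stated mediators, yet the pre-diagnosis list omits it and nothing else in the article brings it back.

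The consequence is possible residual socioeconomic confounding, not demonstrated bias. If HRT users are less deprived and deprivation raises the death hazard, the five-group illustration puts a null hazard ratio at about 0.99 to 0.95 before any other adjustment. If the gradient ran the other way, so would the shift. Moderate importance is the right level. The evidence does not show that the analysis would be invalid without the change, so it should not be presented as an essential correction.

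**What to change.** Add deprivation (the relevant Index of Multiple Deprivation) to the covariates of the pre-diagnosis Cox model in Scotland and Wales. Apply this to cancer-specific mortality and to all-cause mortality and second cancers wherever that model is repeated. Relative to the post-diagnosis model, only stage, grade and treatment would then be dropped, with medication use taken before diagnosis. If deprivation was left out on purpose, the plan should give the reason.

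The cardiovascular and VTE models can stay as they are. The cost is one added term in the covariate sentence. The variable is already on the list to be identified in both cohorts, and no stated sample size or power figure changes. The edit should be made before analysis, so that the adjustment is prespecified.

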### Outcome

The primary outcome will be cancer-specific mortality (based upon cancer as the underlying cause of death) from national mortality records (see Table 1). Secondary outcomes of all-cause mortality (from mortality records), any second cancer (and by type, from cancer registry records), and cardiovascular disease (from hospital admissions data or mortality records) including separately coronary heart disease, stroke, VTE and any cardiovascular disease (based upon coronary heart disease or stroke), will also be investigated.

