The primary analysis strategy will be repeated for the secondary outcome of all-cause mortality and second cancers. A different analysis strategy will be used to investigate the secondary outcome of cardiovascular disease and VTE. In these analyses current use of hormone replacement therapy after cancer diagnosis will be modelled as a time-varying covariate. Patients will become a current user upon the date of each hormone replacement therapy prescription, and remain a user for the duration of the prescription, based upon the daily defined dose, plus 30 days to account for any residual effect. The exposure period from the end of one prescription plus 30 days to the start of the next will be allocated to past use. Cox regression models will then be used to calculate HRs and 95% CI for cardiovascular disease overall and by type comparing hormone replacement therapy current use and past use to non-users, adjusting for the confounders mentioned previously.

In general, multiple imputation will be used to impute missing values particularly for stage, smoking and BMI. As recommended cancer-specific death status and cumulative hazard will be included in imputation models [41], along with exposure and confounder variables and results will be combined using Rubin’s rules. STATA 16 will be used for all analyses.

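### If the pre-diagnosis HRT analysis is repeated for second cancers, as the text suggests, follow-up starts at the first diagnosis and tumours already present count as events

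*Protocol article*

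**What the plan says.** The Statistical analysis section of the protocol article sets out the design: "Two main analyses will be conducted investigating HRT use after diagnosis and immediately before diagnosis". The two have different starting points. For HRT after diagnosis, "patients will be followed from 6 months after cancer diagnosis to cancer-specific mortality", and as a result "patients who died from any cause in the first 6 months after cancer diagnosis will be excluded". For the other, "In the analysis of HRT before diagnosis, cancer patients will be followed from diagnosis to cancer-specific mortality".

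The Outcome section defines the secondary outcome at issue as "any second cancer (and by type, from cancer registry records"), with no minimum interval from the first cancer. Its analysis is given in one sentence: "The primary analysis strategy will be repeated for the secondary outcome of all-cause mortality and second cancers". The text then sets up a separate approach for cardiovascular disease and VTE, based on current and past use of HRT after diagnosis. Second cancers get no start date of their own.

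**The concern.** Starting the clock at diagnosis suits death, because every woman is alive on that day. It does not suit second cancers. A second primary can already exist at that point and come to light through the imaging, biopsies or surgery done for the first tumour. With follow-up from day 0, these tumours enter as events in the first weeks.

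The article's secondary aim is the association of HRT with second cancers in women who have cancer. A tumour present at time zero cannot inform risk after the first cancer. It reflects incidence before the first diagnosis and how intensively the woman was investigated. If such tumours are unrelated to prior HRT, they pull the hazard ratio towards 1. If they are related, they move it in the direction of that relation. The Background section makes a relation conceivable: it cites lower risks of liver cancer, non-Hodgkin lymphoma and colorectal cancer with HRT, and higher risks of glioma and meningioma with oestrogen-only HRT.

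**Working it through.** **1. Does the pre-diagnosis analysis apply to second cancers?** The text names two main analyses and then repeats the primary strategy for all-cause mortality and second cancers. Only cardiovascular disease and VTE are given another design. So the article changes the design where the authors thought an outcome needed it, and it left second cancers with the mortality design. The natural reading is that both main analyses are repeated, but no sentence says so.

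**2. Does any printed rule remove tumours present at time zero in that analysis?**

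- Cohorts section: excludes women with an earlier invasive cancer. This does not reach a tumour found at or just after the first diagnosis.
- Outcome section: no minimum interval and no rule for synchronous tumours.
- Six-month gap before diagnosis: "HRT use will be identified in the 18 months before diagnosis excluding HRT use in the six months immediately before diagnosis". This lags the exposure, not the outcome.
- Sensitivity analyses with lags of 1 and 2 years: these are for HRT after diagnosis only.
- Adjustment: "Stage, grade and cancer treatments will be excluded from the models investigating HRT before diagnosis, as these could lie on the causal pathway". The model therefore holds no measure of disease extent or treatment that might track intensity of work-up.

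None of these removes such tumours.

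**3. The plan's own figures.** The only power figures are for cancer-specific mortality with HRT after diagnosis. With Schoenfeld's formula, power = Φ(|ln HR| × √(D·p·(1−p)) − 1.96), and p = 0.07:

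- Colorectal, D = 6820, HR 1.15: 0.1398 × √(6820 × 0.0651) − 1.96 = 0.985, power 83.8%.
- Gastric, D = 1181, HR 1.45: 0.3716 × √(1181 × 0.0651) − 1.96 = 1.298, power 90.3%.

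Both agree with the stated value of over 80%. Neither depends on when second-cancer follow-up starts. The article gives no expected number of second cancers.

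**4. Dilution (assumed inputs).** Let f be the share of counted second cancers already present at diagnosis and unrelated to HRT. Then approximately HR observed = (1 − f) × HR true + f.

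| f | True HR 1.50 | True HR 0.80 | True HR 1.00 |
|---|---|---|---|
| 10% | 0.9 × 1.50 + 0.1 = 1.45 | 0.9 × 0.80 + 0.1 = 0.82 | 1.00 |
| 20% | 0.8 × 1.50 + 0.2 = 1.40 | 0.8 × 0.80 + 0.2 = 0.84 | 1.00 |
| 40% | 0.6 × 1.50 + 0.4 = 1.30 | 0.6 × 0.80 + 0.4 = 0.88 | 1.00 |

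Mixing on the log scale instead, ln HR observed = (1 − f) × ln HR true, shows the same pattern: a true HR of 1.30 becomes 1.27, 1.23 and 1.17 for f of 10%, 20% and 40%.

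**5. Shift (assumed inputs).** Suppose the early tumours have their own hazard ratio with prior HRT, and later second cancers have a true HR of 1. Then ln HR observed = f × ln HR early. For an early HR from 0.7 to 1.5, the observed HR runs from 0.97 to 1.04 at f = 10% and from 0.87 to 1.18 at f = 40%.

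**The case against.** The strongest reply is that the pre-diagnosis analysis may not be meant at all. The repeated strategy is named in the singular, the Abstract describes the post-diagnosis model first and the pre-diagnosis one as a repeat, and the power calculation covers post-diagnosis use only. If the phrase means the post-diagnosis analysis alone, follow-up starts at 6 months and the difficulty disappears. This stands as a condition on the point: the plural main analyses favour the wider reading but do not settle it.

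A second reply is that rules for synchronous tumours are detail that an article may leave to the full protocol. This stands in part, since such a rule may exist there. But the article does more than stay silent: it fixes a start date and carries it over to an outcome that it does not fit.

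A third is that no harm is shown. This is right as to size, because the early share and its relation to HRT are both assumed.

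A reader might go further and infer three things that the documents do not support:

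- **That the post-diagnosis analysis has the same fault, because its early exclusion mentions only deaths.** That exclusion follows from starting follow-up at 6 months and is worded for the outcome under discussion. In a time-to-first-event model, a woman whose second cancer precedes entry is not at risk. The length of the initial period and the lag are also to be varied there.
- **That metastases will be registered as new primaries.** Nothing in the article suggests this, and it describes its registry data as of high quality.
- **That the hazard ratio is known to be distorted.** It may be diluted or shifted; the documents give nothing from which to establish either.

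**Conclusion.** The point holds on a condition: if the two main analyses are both repeated for second cancers, the printed plan starts the pre-diagnosis analysis at the first diagnosis and counts tumours that were already there. The likely effect is dilution. With assumed early shares of 10% to 40% unrelated to HRT, a true HR of 1.50 is seen as 1.45 to 1.30, and a true HR of 1 is unchanged. A shift away from the true value needs early tumours to differ by prior HRT use, which is possible but not shown.

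The reach is narrow: one secondary outcome in one of two analyses. Cancer-specific mortality, all-cause mortality, the cardiovascular and VTE analyses and the power calculation are not affected. It is still worth correcting, because none of the planned sensitivity analyses described in the article would reveal it.

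**What to change.** In the secondary-outcome paragraph of the Statistical analysis section, say whether the pre-diagnosis HRT analysis is run for second cancers. If it is, add that for this outcome:

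- follow-up starts 6 months after the first diagnosis, as in the post-diagnosis analysis;
- women who died or had a second cancer registered before that date are excluded, and the number excluded is reported;
- the analysis is repeated with a 12-month start.

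This takes a sentence or two and uses registry and death dates that the study already plans to hold. The cost is fewer second-cancer events. The estimate then applies to women alive and free of a second cancer at 6 months. In the article's colorectal example about 20% (4400 of 22,000) die before that point, but each of those women could have contributed at most 6 months of follow-up.

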### HRT and cardiovascular disease

Studies in the general population have observed that women taking HRT have increased risks of various cardiovascular diseases including coronary heart disease [29], stroke [30] and venous thromboembolism (VTE) [31], particularly in the first years of use [29]. VTE is of particular concern as cancer patients are already at increased risk [32] and it is a common cause of death in cancer patients [33]. Despite this evidence, the risk of cardiovascular disease, and VTE, in cancer patients using HRT has not been investigated previously in large epidemiological cohorts.

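### The main CVD/VTE model builds current and past use only from HRT after diagnosis, so starters and continuing users share one state and women who stopped before diagnosis appear to join the reference group

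*Protocol article*

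**What the plan says.** In the Protocol article, Statistical analysis, the primary strategy is carried over to all-cause mortality and second cancers only. Cardiovascular disease and VTE are given a strategy of their own, whose exposure is defined thus: "In these analyses current use of hormone replacement therapy after cancer diagnosis will be modelled as a time-varying covariate". The states are then fixed by two rules. For current use: "Patients will become a current user upon the date of each hormone replacement therapy prescription", lasting for the prescription's duration plus 30 days. For past use: "The exposure period from the end of one prescription plus 30 days to the start of the next will be allocated to past use". The model works by "comparing hormone replacement therapy current use and past use to non-users, adjusting for the confounders mentioned previously".

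The confounders referred to are those of the post-diagnosis mortality model, described as "adjusting for age, year, ethnicity, stage, cancer treatment, grade, comorbidities, prior hysterectomy/oophorectomy, medication use (as time-varying covariates) and deprivation". HRT before diagnosis is not among them.

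Higher up in the same section, among the additional analyses, the plan includes a new-user design, "restricting analyses to cancer patients who did not use HRT before diagnosis [40", a version adjusted for HRT before diagnosis, and an analysis of when HRT was started after diagnosis. None of the three names an outcome.

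The Background (HRT and cardiovascular disease) reports raised cardiovascular risks with HRT in the general population, "particularly in the first years of use [29", and singles out VTE as a concern in women with cancer.

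**The concern.** The rules treat every post-diagnosis prescription alike. A first-ever prescription and the latest of many both open current use, so one hazard ratio averages women entering the period of highest risk with women who may already have come through it. On the natural reading, a woman who used HRT up to diagnosis and then stopped never leaves the non-user state, although in substance she is a past user.

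This sits badly with the Background's emphasis on the first years of use. The Discussion promises evidence to help patients and clinicians decide whether to use HRT. For a woman thinking of starting, an average dominated by continuing users could look more reassuring than her own risk warrants, and this concerns the outcomes on which the plan itself voices a safety worry.

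**Working it through.** The plan gives no figure on this point: no CVD or VTE rates, no share of continuing users, no share of women who stopped. Its power statements concern cancer-specific mortality only. The check is therefore a comparison of the rules, followed by an illustration on assumed inputs.

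**Where each type of woman falls under the stated rules**

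| HRT before diagnosis | HRT after diagnosis | State in the CVD/VTE model |
|---|---|---|
| No | Starts | Current user |
| Yes | Continues | Current user, not distinguished from a starter |
| Yes | None | Non-user (implied; no rule stated) |
| No | None | Non-user |

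**Formula.** Let s be the share of current-use time from continuing users and w the share of non-user time from women who stopped before follow-up. Then, approximately,

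observed HR = [(1 − s) × HR(starters) + s × HR(continuing)] / [(1 − w) + w × HR(residual)].

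**Pooling alone (w = 0).** Assume HR 2.0 in starters and 1.2 in continuing users:

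- s = 30%: 0.7 × 2.0 + 0.3 × 1.2 = 1.76
- s = 50%: 0.5 × 2.0 + 0.5 × 1.2 = 1.60
- s = 70%: 0.3 × 2.0 + 0.7 × 1.2 = 1.44
- s = 90%: 0.1 × 2.0 + 0.9 × 1.2 = 1.28

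The result depends heavily on the assumed hazard ratios. At s = 50%, 1.5 and 1.2 give 1.35, and 3.0 and 1.0 give 2.00. If both groups have the same hazard ratio, for example 1.5, the pooled value is 1.5 whatever s is.

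**Women who stopped, in the reference.**

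- w = 5%, residual HR 1.3: the divisor is 0.95 + 0.05 × 1.3 = 1.015, so 1.60 becomes 1.58.
- w = 10%, residual HR 1.5: the divisor is 0.90 + 0.10 × 1.5 = 1.05, so 1.60 becomes 1.52.
- Residual HR 1.0: the divisor is 1 and nothing changes.

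**Earlier VTE (secondary point).** If earlier VTE were not adjusted for, the HRT hazard ratio would be multiplied by [1 + p1(R − 1)] / [1 + p0(R − 1)]. Here p0 and p1 are the prevalence of earlier VTE in non-users and users, and R is its effect on the VTE hazard. Assume p0 = 5%, p1 one third to one half of p0, and R = 3 to 5:

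- Strongest case: (1 + 0.0167 × 4) / (1 + 0.05 × 4) = 1.067 / 1.20 = 0.89
- Weakest case: (1 + 0.025 × 2) / (1 + 0.05 × 2) = 1.05 / 1.10 = 0.95

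**The case against.** A reader might infer that the plan ignores pre-diagnosis HRT altogether. It does not. The new-user restriction and the adjustment for earlier HRT are worded for HRT after diagnosis in general, and the CVD/VTE analysis is one of those. Against that, they stand among additions to the mortality analyses, before the separate strategy is introduced. Coverage is therefore ambiguous rather than absent. Even if they do apply, the main current/past/non-user comparison stays as written.

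A reader might also take it as settled that women who stopped count as non-users and that harm will be diluted. Neither is established. The first is an implication of defining exposure after diagnosis; no rule says so. The second is conditional, as the working shows. The Background's remark on early use carries the reference cited for coronary heart disease, not the one for VTE, although the sentence can be read as covering all three outcomes.

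Three further points stand:

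- Starting versus continuing is not the same as early versus late. A continuing user may have begun shortly before diagnosis, and a starter eventually leaves her first years of use. An 18-month look-back cannot fully separate the two.
- An average over current users is a legitimate quantity, since deciding whether to use HRT includes deciding whether to continue.
- It is tempting to add that supply issued before diagnosis is misclassified. That depends on when CVD/VTE follow-up begins, which is not stated. If it begins 6 months after diagnosis, supply shorter than about 5 months plus 30 days would have lapsed.

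On prior events, Covariates lists relevant comorbidities in open-ended terms, and comorbidities are in the adjustment set. Earlier heart disease or stroke may well be covered, so their omission cannot be claimed. Earlier VTE is not named as a covariate.

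The point is not just detail that an article leaves to a fuller plan. The article sets the exposure states down to a 30-day window, and that definition leaves out status before diagnosis.

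**Conclusion.** The point holds in a limited form. As written, the main CVD/VTE model sets current and past use from post-diagnosis HRT alone. It merges starters with continuing users, and by implication puts women who used HRT only before diagnosis in the reference group. The planned new-user and adjusted analyses are not clearly extended to these outcomes.

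If risk is higher early in use, or past use carries residual risk, the current-use hazard ratio would understate the risk for a woman starting HRT. The size cannot be derived from the document. The 1.76 to 1.28 range for an assumed starter hazard ratio of 2.0, the further 1.5% to 5% fall from stoppers, and the 0.89 to 0.95 factor for earlier VTE all rest on assumed inputs and show scale only. The outcomes are secondary and the cancer-mortality analysis is untouched, but the change is cheap and should be made.

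**What to change.** Amend the CVD/VTE paragraph of Statistical analysis as follows.

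1. Use the pre-diagnosis prescriptions to set each woman's state at the start of follow-up. The before-diagnosis analysis already looks back 18 months; here the last 6 months before diagnosis, which that analysis leaves out, should be included. Women who used HRT only before diagnosis then become past users, and non-user means no use in the look-back. State when follow-up begins for these outcomes.
2. Report current use separately for women starting after diagnosis and for continuing users, by time since initiation where records reach far enough back. State that the new-user analysis also covers CVD and VTE.
3. As a secondary matter, name earlier VTE in the adjustment set, or exclude women with an earlier record of the outcome being analysed.

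The before-diagnosis analysis already draws on prescriptions from this period, so the cost is mainly extra coding. The price in precision is smaller numbers and wider intervals among new starters.
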